# Efficacy and safety of XELOX combined with anlotinib and penpulimab vs XELOX as an adjuvant therapy for ctDNA-positive gastric and gastroesophageal junction adenocarcinoma: a protocol for a randomized, controlled, multicenter phase II clinical trial (EXPLORING study)

**DOI:** 10.3389/fimmu.2023.1232858

**Published:** 2023-10-31

**Keywords:** clinical trial, GA/GEJA, anlotinib, penpulimab, XELOX adjuvant chemotherapy, CtDNA, vascular normalization, protocol

## Abstract

**Background:**

The efficacy of current adjuvant chemotherapy for gastric adenocarcinoma/gastroesophageal junction adenocarcinoma (GA/GEJA) leaves much to be desired. ctDNA could serve as a potential marker to identify patients who are at higher risk of recurrence. Reinforcing standard adjuvant chemotherapy with immunotherapy has already been indicated to significantly improve clinical outcome, albeit such evidence is rare in GA/GEJA. Here, we intend to explore the clinical benefit of the reinforcement of adjuvant immunotherapy and antiangiogenics alongside with chemotherapy in patients who are deemed in high risk of recurrence by ctDNA analysis, which might shed light on further improvements in adjuvant therapy for GA/GEJA.

**Methods/Design:**

This study is designed as a prospective, multicenter, randomized, controlled phase II study in patients histologically or cytologically diagnosed with GA/GEJA who underwent D2 gastrectomy and achieved R0 or R1 resection. From February 2022, a total of 300 stage III patients will be enrolled and subjected according to ctDNA sequencing results, and those with positive results will subsequently be randomized 1:1 to arm A or B. Patients in arm A will receive anlotinib, penpulimab and XELOX for 6-8 cycles, maintained with anlotinib and penpulimab for up to 1 year, while patients in arm B will receive XELOX alone for 6-8 cycles. ctDNA-negative patients will be assigned to arm C, and patients who are ctDNA positive but failed in randomization will be assigned to arm D. Patients in arms C and D will receive the investigator’s choice of therapy. The primary endpoint is the median disease-free survival (DFS) of arm A versus arm B determined via CT/MRI imaging. Secondary endpoints include the DFS of ctDNA positive patients versus ctDNA negative patients, the 2- and 3-year DFS rates, overall survival (OS), the impact of hallmark molecules on the treatment response, adverse events (AEs), and the impact of nutrition status or exercise on recurrence.

**Discussion:**

We expect that ctDNA would be a strong prognostic factor and ctDNA-positive patients are at higher risk of relapse than ctDNA-negative patients. The addition of anlotinib and penpulimab to XELOX, may contribute to delaying relapse in ctDNA-positive patients.

**Trial registration:**

https://www.clinicaltrials.gov, identifier NCT05494060.

## Background

1

Gastric cancer (GC) is a malignant tumor occurring in the digestive tract; it ranks fifth in occurrence among all malignancies and third in mortality. Chinese GC patients constitute 47% of patients worldwide (1). There were approximately 478,000 new occurrences and 374,000 fatalities in China in 2020, and the occurrence and fatality of GC rank third among all malignancies in the Chinese population (2). For stage II patients, the recommended regimen is S-1 alone (per oral to 1 year after surgery) or capecitabine plus oxaliplatin/cisplatin (3, 4). In 2022, the 3-year follow-up report of the JACCRO GC-07 trial suggested administering 6 cycles of docetaxel with S-1 (DS regimen) in stage III GC patients which improved the OS of patients compared to single-regimen S-1 (5). In 2019, the RESOLVE trial showed that for cT4aN+M or cT4bNxM locally advanced GC, adjuvant chemotherapy with 8 cycles of the S-1 with oxaliplatin (SOX) regimen is noninferior to the XELOX regimen (6). The 3-year DFS of patients enrolled in these trials is approximately 50% - 85%. However, for stage III patients, the 3-year DFS is approximately 50% - 65%, which implies a significant risk of recurrence in patients receiving standard postoperative adjuvant chemotherapy.

The identification of patients who are most at risk and the precise administration of reinforced therapy are the focus in further improving the perioperative treatment. Circulating tumor DNA (ctDNA) is a biomarker with promising prospects of serving as a prognostic indicator. Kotani et al. reported that postsurgical ctDNA in patients with stage II–IV resectable CRC is found to be associated with higher recurrence risk (hazard ratio (HR) 10.0, *P* < 0.0001). Furthermore, postsurgical ctDNA positivity identified patients with stage II or III CRC who derived benefit from adjuvant chemotherapy (HR 6.59, *P* < 0.0001) (7). In addition, Gale et al. used ctDNA as an indicator for risk of relapse in localized non-small cell lung cancer (NSCLC) following treatment with curative intent. Detection within 2 weeks to 4 months after treatment was associated with shorter recurrence-free survival [hazard ratio (HR): 14.8, *P<*0.00001] and OS (HR: 5.48, *P<*0.0003) (8). In GC, Yang et al. reported a significant correlation of worse DFS and OS. (HR = 14.78, 95%CI, 7.991–61.29, *P* < 0.0001 and HR = 7.664, 95% CI, 2.916–21.06, *P* = 0.002, respectively), and preceded radiographic recurrence by a median of 6 months (9). From these studies we can conclude that positive ctDNA is a sensitive risk indicator for recurrence and calls for reinforced means to mitigate this risk. However, the number of patients participating in studies on the value of ctDNA as a risk indicator of recurrence in postoperative GC patients was rather limited, calling for additional verification. Studies supporting the use of immune checkpoint inhibitors (ICIs) in the adjuvant setting in gastroesophageal cancer are also rare. The results of CheckMate-577 revealed that disease-free survival (DFS) was significantly longer in nivolumab group than in placebo group in GA/GEJA patients (HR for disease recurrence or death, 0.69; 96.4% CI, 0.56 to 0.86; *P<*0.001) (10). Similar researches also suggest a benefit in ICIs adjuvant therapy, such as the CheckMate-274 trial in urothelial cancer (11) and the MAGE-A3 trial in NSCLC (12). In summary, the value of ctDNA as a risk factor and the clinical benefit of ICIs as a part of adjuvant therapy requires further evidence.

Therefore, we designed this clinical trial, providing ctDNA screening to stage III GC patients who underwent curative gastrectomy, and randomized them into different arms based on ctDNA results. The trial arm will be treated with chemotherapy combined with ICIs and antiangiogenics. The control arm will be given standard chemotherapy. We hope to further explore the prognostic value of ctDNA and whether reinforced adjuvant treatment for ctDNA-positive patients can improve the prognosis.

## Patients and methods

2

### Recruitment and allocation

2.1

Patients with pathologically and/or cytologically diagnosed GA/GEJA who underwent D2 gastrectomy were potentially eligible for enrollment, and every consenting patient signed the informed consent form (ICF) prior to actual enrollment.

The criteria for eligible patients included 18- to 75-year-old males and females (female participants should not be pregnant or lactating), patients histologically or cytologically diagnosed with stage III GA/GEJA (Siewert III), patients who underwent D2 gastrectomy and achieved R0 or R1 resection, patients with an Eastern Cooperative Oncology Group (ECOG) performance status between 0 to 1, and patients without significant defects in organ function. Considering that the detection of ctDNA via next-generation sequencing (NGS) may take up to 10 working days, patients who received only the first cycle of XELOX chemotherapy will also be accepted for enrollment. The major exclusion criteria included serious/uncontrollable hypertension/cardiac insufficiency/infection/diabetes/renal insufficiency, tendency for gastrointestinal hemorrhage, immune deficiency, recent thrombotic event or any other situation deemed unsuitable for enrollment by the researcher. A more detailed version of our inclusion/exclusion criteria is provided in **Supplementary Materials**.

The recruited patients will be subjected to ctDNA analysis (Geneseeq Technology Co., Ltd., Nanjing, China; 1021 genes NGS) 3-8 weeks after the operation. Patients with positive ctDNA will be randomly allocated to two arms (arms A&B). Patients with negative ctDNA will constitute arm C. Patients who are ctDNA positive but for various reasons fail in random allocation will be assigned to arm D.

Block randomization is used in this study, with a block size of 4. Random allocation sequence including randomization seed, block size and block counts are provided by our statistics specialist. A central randomization is established, in which researchers will enter the participants’ general information, including abbreviation of participant’s name, gender and age to apply for a randomization number and allocation into arms. This randomization number will be included in the participant’s medical history, and the participant will receive treatment according to the allocated arm.

### Trial design

2.2

This study was designed as a prospective, multicenter, randomized, controlled, open-label and multicenter phase II clinical trial conducted in China. beginning in June 2022. Patients in arm A (experiment group) will undergo XELOX chemotherapy combined with anlotinib and penpulimab until they reach the 6-8 cycle without recurrence. Subsequently, they will receive anlotinib combined with penpulimab as maintenance therapy until recurrence or death occurs or reach the maximum length of 1 year. Patients in arm B (control group) will undergo XELOX chemotherapy for 6-8 cycles. Arm C&D will receive the researcher’s choice of treatment according to recommendations by the Chinese Society of Clinical Oncology (CSCO) guidelines. All ctDNA positive patients should receive ctDNA tests every 3 months as a dynamic monitoring procedure. Considering that NGS analysis may take up to 10 working days, patients could receive 1 cycle of XELOX chemotherapy after ctDNA sampling. Follow-ups and evaluations will be carried out regularly. In addition to data concerning treatment and recurrence, data on nutritional and exercise habits will also be collected in an exploratory attempt to determine the impact of nutrition and exercise on survival and the risk of recurrence.

The primary endpoint of our trial is the DFS of ctDNA-positive patients receiving XELOX combined with anlotinib and penpulimab versus ctDNA-positive patients receiving XELOX alone (arm A versus arm B). The secondary endpoints include the DFS of ctDNA-positive patients versus ctDNA-negative patients, the 2-year DFS rate, the 3-year DFS rate, overall survival (OS), the relationship of dynamic ctDNA status and treatment response, adverse events (AEs), and the impact of nutrition status and exercise on recurrence.

### ctDNA sequencing via NGS

2.3

ctDNA from the plasma was extracted using a QIAmp Circulating Nucleic Acid Kit (Qiagen). Genomic DNA from surgical tumor samples and white blood cells was extracted using a DNeasy Blood & Tissue kit (Qiagen). Purified genomic DNA was qualified by Nanodrop2000 for A260/280 and A260/A230 ratios (Thermo Fisher Scientific). All DNA samples were quantified by Qubit 3.0 using the dsDNA HS Assay Kit (Life Technologies) according to the manufacturer’s recommendations. Hereafter, a local bioinformatics polishing pipeline was used to identify somatic variants in ctDNA after filtering out germline variants using normal control DNA. Mutations identified in the matched tumor DNA, which were supported by a minimum of one unique consensus mutant allele read and passed the polishing criteria, were regarded as being present.

### Intervention and assessment

2.4

Arm A (experimental group) will be given anlotinib 12 mg, po, qd + penpulimab 200 mg, iv, d1 + XELOX regimen (oxaliplatin 130 mg/m^2^, iv, d1 + capecitabine 1000 mg/m^2^, po, qd, d1-14). Arm B will be given the same XELOX regimen as arm A. Arms C&D will be given the investigator’s choice of treatment. If drug-associated toxicity occurs during treatment, it is up to the investigator to consider the effect of the toxicity (according to the National Cancer Institute (NCI) Common Terminology Criteria for Adverse Events (CTCAE 5.1) and the therapeutic benefit and decide whether to adjust the dose of anlotinib or penpulimab. The starting dose of anlotinib is 12 mg qd and can be decreased to 10 mg or 8 mg. A dose reduction or suspension is allowed only when ≥ grade 3 hematological toxicity or ≥ grade 2 nonhematological toxicity is observed. Regarding penpulimab, adjustment of the dose is not recommended. Management of the AEs of penpulimab should be in accordance with the CSCO guidelines for the management of immune checkpoint inhibitor-related toxicity. If the administration of penpulimab is postponed for more than 12 weeks due to infusion-related AEs or more than 3 weeks due to immune-related AEs, the usage of penpulimab should be permanently discontinued. The study flowchart is shown in **Supplementary Materials Figure 1**. Supportive treatment including antibiotics, pain reliefs, steroids, palliative surgery is considered acceptable as a concomitant care. Any other anti-tumor chemo/endocrine/immune treatment is considered not acceptable.

The results of follow-up examinations should be closely monitored (see **Supplementary Materials** for details), including ctDNA status every 3 months (in ctDNA-positive patients only) and nutrition status, in a case report form (CRF). Imaging via CT or MRI will be performed before the first administration of drugs, after every 2 cycles and upon treatment completion. Upon and after treatment completion, patients will still be regularly followed-up for survival.

### Data collection and management

2.5

After obtaining ICFs signed by the patients, our clinical investigators will begin collecting the baseline data, including age, gender, body mass index and adverse events, along with all laboratory indices and imaging that are required (refer to “Intervention and Assessment” & **Supplementary Materials** for further details). Peripheral blood and tissue samples will be collected for cytometry analysis, immune environment analysis and genetic sequencing.

All clinical data relevant to our patients will be recorded in CRFs on a regular basis by trained and independent clinical research coordinators (CRCs) and managed by a data manager based at the main center. All data will be verified by the data manager and the principal investigator. The CRFs will be under constant surveillance by the clinical investigators to minimize the possibility that any mistake remains unchecked. All research data will be available exclusively to researchers who have signed a confidential disclosure agreement. In particular, any collected information in this study that may potentially lead to the disclosure of any patient’s identity will not be released until consented by the patient, unless special urgent or legal circumferences dictate otherwise. Should any potential error or missing in the data be identified, the rectification will be made only under the approval of the principal investigator, collaborator, statistician and data manager. The ethics committees of the First Affiliated Hospital of Nanjing Medical University will enforce the rights and welfare of all the patients, adherence to the approved version of the protocol, proper practices in collecting clinical data and performing statistical analysis, and anonymity in publications.

### Statistical analysis

2.6

Previous research reported that the median DFS of postoperative adjuvant chemotherapy in ctDNA-positive GA/GEJA patients is approximately 12 months (13, 14). Our hypothesis is that anlotinib plus penpulimab combined with XELOX will prolong DFS to 24 months. Setting the single-sided α as 0.05, β as 0.2, the length of in-group time as 18 months and the length of follow-up as 24 months, the calculated sample size is 36 patients for the test group (arm A) and 36 patients for the control group (arm B); presuming that the drop-off rate is 10%, the total number of participants needed is 40 each group. The key secondary endpoint is the difference in DFS between ctDNA-positive and ctDNA-negative patients treated by only chemotherapy. Given that the median DFS of ctDNA-negative patients receiving standard treatment is approximately 36 months, two-sided α = 0.05, β = 0.2, the length of in-group time is 18 months, and the length of follow-up is 36 months, the sample size should be 14 each for the ctDNA-positive group and the ctDNA-negative group. Taking both hypotheses into consideration, we presume at least 80 ctDNA-positive patients would be needed to complete this study. Considering that the positive rate of ctDNA in postoperative GA/GEJA patients is approximately 25-30%, a total of 300 participants needs to be screened.

Statistical analysis will be carried out by statistics specialists who will take part in the study during the whole process, from the study design and implementation to the data analysis phase. Measurement variables will be analyzed by means of *t test*, paired *t test*, rank-sum test, paired rank-sum test, analysis of variance (ANOVA), etc. Count variables will be analyzed using the Cochran–Mantel–Haenszel (CMH) chi-squared test, logistic regression and Fisher’s exact test. Ordinal variables will be analyzed via the rank-sum test. Survival data will be compared via the Kaplan–Meier method or Cox regression. The main clinical response indicators will be subjected to per-protocol population (PP) and full analysis set (FAS) analyses simultaneously. A two-sided test for significance was performed as the default, and *P<*0.05 was considered significant. The analysis will be performed using SAS software. The data analysis is planned to be at mid-term and upon completion of this trial.

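### The primary DFS comparison is sized at one-sided alpha 0.05, but the stated default test is two-sided at P<0.05; if that default applies to it, power is about 71% to 75%, not 80%

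*Protocol article*

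**What the plan says.** All the relevant text is in section 2.6 (Statistical analysis) of the protocol article, apart from the 1:1 allocation, which is in the abstract.

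- **Sizing of the primary endpoint.** The control assumption is that the "median DFS of postoperative adjuvant chemotherapy in ctDNA-positive GA/GEJA patients is approximately 12 months"; the hypothesis is that "anlotinib plus penpulimab combined with XELOX will prolong DFS to 24 months". The error rates are set by "Setting the single-sided α as 0.05, β as 0.2", and the time frame by "the length of in-group time as 18 months and the length of follow-up as 24 months". The result is 36 per arm, and then "presuming that the drop-off rate is 10%, the total number of participants needed is 40 each group".
- **Sizing of the key secondary endpoint.** The comparison of ctDNA-positive with ctDNA-negative patients is sized at a two-sided alpha of 0.05, so the two endpoints are given different sidedness.
- **Analysis rule.** The next paragraph says "A two-sided test for significance was performed as the default" and takes P below 0.05 as significant. It does not say that the primary DFS test is one-sided.

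**The concern.** A sample size delivers its stated power only if the test is run at the alpha used to size it. Here the sizing paragraph uses one-sided 0.05 for the primary comparison. The general rule that follows is two-sided 0.05, which in the direction of benefit means one-sided 0.025. Nothing in the article says which of the two decides the primary endpoint.

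The trial's main conclusion depends on the answer. If the two treatments are truly equal, the chance of a false claim in favour of arm A is 5% under one rule and 2.5% under the other. If the planned effect is real, the chance of success differs by about 10 percentage points. For a band of observed results, the same data would be positive under one rule and negative under the other.

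**Working it through.** **Inputs (section 2.6; allocation from the abstract).** Median DFS 12 months in arm B and 24 months in arm A; 18 months accrual; 24 months follow-up; 1:1 allocation; beta 0.2; one-sided alpha 0.05 for sizing; two-sided 0.05 as the analysis default.

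**Assumptions added here.** Exponential DFS (so the hazard ratio is 12/24 = 0.5), uniform accrual, 24 months of follow-up after the last entry, and one analysis at the full alpha.

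**Step 1: event probabilities.** With hazard λ = ln 2 / median, accrual A = 18 and follow-up F = 24:

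p = 1 − [exp(−λF) − exp(−λ(A+F))] / (λA)

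- Arm B: 1 − (0.2500 − 0.0884)/1.0397 = 0.845
- Arm A: 1 − (0.5000 − 0.2973)/0.5199 = 0.610
- Sum 1.455, mean 0.727

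**Step 2: reproduce the plan's figure.** Schoenfeld's formula for the number of events at 1:1 allocation is d = 4(z_α + z_β)² / (ln HR)².

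- One-sided 0.05: 4 × (1.645 + 0.842)² / 0.4805 = 51.5, so 52 events. Then 52/1.455 = 35.7, so 36 per arm, and 36/0.9 = 40. Both stated figures reproduce.
- Two-sided 0.05: 4 × (1.960 + 0.842)² / 0.4805 = 65.4, so 66 events. Then 66/1.455 = 45.4, so 46 per arm, or 52 after 10% drop-off (46/0.9 = 51.1).

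Other standard formulas give 36.3 to 38.5 per arm one-sided, and Schoenfeld and the others together give 45.4 to 48.8 two-sided. Reading the 24 months as total study time gives about 57 to 62 per arm even one-sided. The stated 36 therefore comes from the one-sided alpha with 24 months of follow-up after accrual ends.

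**Step 3: power under each rule.** Power = Φ(√(d/4) × ln 2 − z_α).

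- 36 evaluable per arm: d = 36 × 1.455 = 52.4, and √(52.4/4) × 0.693 = 2.509. One-sided: Φ(2.509 − 1.645) = 80.6%. Two-sided: Φ(2.509 − 1.960) = 70.8%.
- 40 per arm with no loss: d = 40 × 1.455 = 58.2, and √(58.2/4) × 0.693 = 2.644. One-sided: Φ(0.999) = 84.1%. Two-sided: Φ(0.684) = 75.3%.

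| Patients per arm | Expected events | Power, one-sided 0.05 | Power, two-sided 0.05 |
|---|---|---|---|
| 36 evaluable | 52.4 | 80.6% | 70.8% |
| 40, no loss | 58.2 | 84.1% | 75.3% |

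A log-rank simulation of 20,000 trials gave 80.9% and 70.8% for 36 per arm, and 83.8% and 75.1% for 40. With 36 per arm, the other formulas put the two-sided power at 67% to 70%.

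**Step 4: where the two rules disagree.** The largest observed hazard ratio that succeeds is about exp(−2z_α/√d). With d = 52.4 and √d = 7.24:

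- One-sided 0.05: exp(−3.29/7.24) = 0.635
- Two-sided 0.05: exp(−3.92/7.24) = 0.582

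If the planned effect is true, the chance of a result between these limits is 80.6% − 70.8% = 9.8%.

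**The case against.** The strongest reply is that a default applies only where nothing else is specified, and section 2.6 does specify something else for this comparison. It sets a one-sided alpha for the primary endpoint and a two-sided alpha for the key secondary endpoint, which looks like a deliberate distinction. On that reading the specific rule governs the primary test, the default governs the rest, and the plan delivers its 80%. A one-sided 0.05 is also openly declared in the sizing, in a phase II trial that describes its own scale as limited.

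Much of this stands. A reader might infer that the primary test simply has 71% power. The article does not support that without the condition that the two-sided default governs the primary test. What remains is that the one-sided alpha appears only as an input to the sample size, and the paragraph that states how results will be judged carries no exception for the primary endpoint.

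A second reply is that 71% is the low end. It counts the 10% drop-off as contributing nothing, although patients lost to follow-up contribute time until they are censored, and a full analysis set is planned. This is right, and it is why a range is given. Even with no loss at all, however, two-sided power stays below 80%.

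A reader might also infer that the threshold would be picked after the data are seen. The article does not show that. The statistical analysis plan is not available here and may already name the sidedness of the primary test.

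**Conclusion.** The point holds as an internal inconsistency in section 2.6. The stated 80% power belongs to a one-sided 0.05 test, while the only written decision rule is a two-sided default at 0.05 with no stated exception. If that default applies to the primary test, power is about 71% with 36 evaluable per arm and at most about 75% with all 40 fully followed. If a one-sided test is intended, the stated power is correct and only the wording needs repair.

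It would be wrong to read this as a sample-size error, because 36 and 40 per arm both follow from the stated inputs.

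The figures rest on the assumptions listed with the calculation. Any allowance for the planned mid-term analysis is a separate matter and is not included.

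**What to change.** Before any analysis, including the mid-term one, state a single rule for the primary endpoint. Either of these resolves it:

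1. DFS in arm A versus arm B is tested one-sided at alpha 0.05 (equivalently two-sided 0.10) and reported with a matching 90% confidence interval; two-sided P below 0.05 applies to all other analyses.
2. The primary test is two-sided at 0.05, and its power is restated as about 71% with 36 evaluable per arm, rising to about 75% with no loss.

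The cost is one sentence in the protocol or analysis plan, and no additional patients. The downside is that the sponsor must openly declare either the looser threshold or the lower power.

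### The 14 per group given for the key secondary DFS comparison does not follow from its stated two-sided 5% alpha and 80% power; those inputs need about 18 per group.

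*Protocol article*

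**What the plan says.** Section 2.6 of the protocol article holds two sample-size calculations in one paragraph.

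- **Primary (arm A against arm B):** median DFS of 24 against 12 months, one-sided alpha 0.05, beta 0.2, 18 months of accrual, 24 months of follow-up. Result: 36 per arm, raised to 40 for 10% drop-out.
- **Key secondary (ctDNA-positive against ctDNA-negative, both on chemotherapy only):** for the positive group, "the median DFS of postoperative adjuvant chemotherapy in ctDNA-positive GA/GEJA patients is approximately 12 months"; for the negative group, "the median DFS of ctDNA-negative patients receiving standard treatment is approximately 36 months". The design parameters are "two-sided α = 0.05, β = 0.2, the length of in-group time is 18 months, and the length of follow-up is 36 months". Result: "the sample size should be 14 each for the ctDNA-positive group and the ctDNA-negative group".

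The paragraph then takes the two calculations together to arrive at 80 ctDNA-positive patients and 300 screened. The next paragraph of the same section makes a two-sided test at P<0.05 the default for the analysis.

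**The concern.** All inputs to the key secondary calculation are printed, so the result can be checked directly, and it looks too small for a two-sided 5% test. The neighbouring primary calculation is one-sided, which suggests how the mismatch could have arisen.

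At stake is the accuracy of a formal power statement for the only endpoint that the article calls key secondary. A reader who takes 14 per group as giving 80% power under the two-sided test would be misled, and cannot tell from the text which alpha produced the number.

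**Working it through.** **Inputs**, all from section 2.6: medians 12 and 36 months; "two-sided α = 0.05, β = 0.2"; accrual 18 months; follow-up 36 months; equal groups. Assumptions not in the text: exponential DFS, uniform accrual, and follow-up counted from the end of accrual.

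**Formulas**

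- Hazard: λ = ln 2 / median.
- Event probability with accrual A and follow-up F: p = 1 − [exp(−λF) − exp(−λ(A+F))] / (λA).
- Schoenfeld events for equal groups: d = 4(z_α + z_β)² / (ln HR)².
- Patients per group: n = d / (p₁ + p₂).

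**Step 1: reproduce the plan's primary figure.** Medians 12 and 24, HR 2, A = 18, F = 24.

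- p = 0.845 and 0.610.
- One-sided 0.05: d = 4(1.645 + 0.842)² / 0.480 = 51.5.
- n = 51.5 / 1.455 = 35.4, so 36 per arm.

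This agrees with the printed 36, which supports both the method and the reading of follow-up as time after accrual ends.

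**Step 2: the key secondary with the same method.** Medians 12 and 36, HR 3, A = 18, F = 36.

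- Positive: p = 1 − (0.1250 − 0.0442) / (0.05776 × 18) = 0.922.
- Negative: p = 1 − (0.5000 − 0.3536) / (0.01925 × 18) = 0.577.
- Sum 1.500; (ln 3)² = 1.207.

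| Alpha | Events d | d / 1.500 | Per group |
|---|---|---|---|
| Two-sided 0.05 (as stated) | 4(1.960 + 0.842)² / 1.207 = 26.0 | 17.3 | 18 |
| One-sided 0.05 | 4(1.645 + 0.842)² / 1.207 = 20.5 | 13.7 | 14 |

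**Step 3: power.** Power = Φ(√(D/4) × ln 3 − z_α), with D the expected events.

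- 14 per group: D = 14 × 1.500 = 21.0. Two-sided: Φ(2.517 − 1.960) = 71.1%. One-sided: Φ(2.517 − 1.645) = 80.8%.
- 18 per group: D = 27.0. Two-sided: Φ(2.854 − 1.960) = 81.4%.

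**Step 4: sensitivity at two-sided 0.05.**

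- Other methods, patients per group: Lakatos log-rank 17.7, log-hazard variance 18.3, Lachin-Foulkes 20.1, Freedman 20.9.
- Simulated log-rank power (8,000 runs): 70.4% with 14 per group, 80.7% with 18.
- If the 36 months is total study time (accrual 18, then 18 more): 22.0 by Schoenfeld and 22.8 by Lakatos, so 22 to 23 per group.
- If every patient is followed for a fixed 54 months, the most generous reading: 16.2, so 17 per group.

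None of these comes within two patients of 14.

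**Step 5: the group sizes the design will produce.** Arm B has about 40 patients. With 25–30% of 300 positive, 75 to 90 are positive and 210 to 225 negative. For 40 against 210, D = 40 × 0.922 + 210 × 0.577 = 158.2, the allocation factor is 0.16 × 0.84 = 0.1344, and power is Φ(√(158.2 × 0.1344) × ln 3 − 1.960) = Φ(3.11), about 99.9%. This uses the full 36-month follow-up and counts every negative patient.

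**The case against.** The strongest objection is that nothing in the trial turns on the figure. The primary comparison fixes the enrolment target, and the trial will have far more than 14 or 18 in each group. That stands. A reader might infer from the 71% that the ctDNA comparison is underpowered; the document does not support this, because 71% applies to 14 per group and the trial will not analyse groups that small.

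Four further limits also stand:

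- One might say that 14 arises only from a one-sided alpha. That is not strictly true. Two-sided, 26.01 events rounded up to 27, halved and rounded up also give 14. That route treats every patient as having an event, ignores the stated accrual and follow-up, and would give 26 rather than 36 per arm for the primary (51.5 / 2 = 25.7). It does not rescue the figure, but the cause remains an inference.
- The equal-group assumption is not an error. The figure reads as a minimum for each group.
- The document ties no early ctDNA read-out to 14 per group; it mentions only an unspecified mid-term analysis.
- Power above 99% for the actual groups is not unconditional. The comparison is restricted to patients treated with chemotherapy only, while arm C receives the investigator's choice (sections 2.2 and 2.4). The Trial status section gives a study length of 18 months. If follow-up were cut at 18 months from the first enrolment (an assumption, not the stated plan), the event probabilities fall to 0.378 and 0.155, and power at 40 against 210 is about 79%.

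**Conclusion.** The printed 14 per group is wrong for its stated error rates. At two-sided 0.05 and 80% power about 18 per group are needed, four more than printed (4/14 = 29%). Fourteen gives about 71% power, nine points below the stated 80%. The agreement with the one-sided answer, by the method that also returns the primary's 36, makes a carried-over one-sided alpha the probable explanation but does not prove it.

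The conclusion rests on exponential DFS, uniform accrual and follow-up counted after accrual. The alternative readings tried give 17 to 23 per group, so it does not depend on the choice. It is an error in a stated figure. It does not show that the trial is too small for this comparison.

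**What to change.** In section 2.6, replace 14 by 18 per group for the key secondary comparison and keep the two-sided alpha of 0.05. Relabelling the 14 as one-sided would be the weaker repair: it rests on a guess about the cause and would set the planning alpha against the section's two-sided default.

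It would help to add that the comparison is expected to use about 40 ctDNA-positive patients (arm B) and up to 210 to 225 ctDNA-negative patients, so it does not drive the trial size. If a power is quoted for these numbers (above 99% by Schoenfeld), state that it assumes the full 36 months of follow-up and that arm C patients qualify as treated with chemotherapy only.

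The cost is one number and, if wanted, one sentence. Enrolment and design do not change.
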